## Methods

### Study Overview

We propose to evaluate the effectiveness and implementation of the Support-Moms app into routine care. We hypothesize that Support-Moms will improve maternity service use and reduce the MMR when integrated into routine care. We will test the effectiveness of the Support-Moms intervention in a randomized controlled design (aim 1); evaluate intervention implementation using the implementation outcomes framework by Proctor et al [66], as outlined in Figure 1 (aim 2); and then refine implementation strategies for future scale-up using the CFIR, as outlined in subsequent sections [67]. We will assess the cost and cost-effectiveness of implementing this intervention into routine care and its implication for sustainability (aim 3). These outcomes will serve as indicators of implementation success or necessary preconditions for attaining desired service outcomes for women in rural, resource-limited settings. This will enable us to identify practical, context-specific, and actionable strategies for achieving optimal implementation effectiveness at a low cost. The intervention strategies were developed in our pilot work together with facility HCPs. In the cost-effectiveness analysis, if Support-Moms and standard of care are found to have equivalent effectiveness, we will conduct a cost-minimization analysis where only the cost of Support-Moms per participant will be estimated and reported (no incremental cost-effectiveness ratios [ICERs] will be calculated). This alternative approach would remain informative to the policy makers and stakeholders in maternity service use. Notably, simultaneous assessment is warranted given the (1) strong preliminary evidence, (2) relatively low investment needed for costing, and (3) overall efficiency of our proposed type 1 hybrid effectiveness-implementation trial approach.

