### Aim 3: Evaluating the Cost and Cost-Effectiveness of Implementing the Support-Moms Intervention Into Routine Care and Its Implication for Sustainability

The incremental cost and the cost-effectiveness of the Support-Moms intervention or program will be estimated from HCP and health system and societal perspectives to guide the decision makers on continuation, incorporation, integration, sustained use, and routinization—a method that has previously been used in a Ugandan context [99]. We will measure and record the cost of developing and implementing the intervention (program costs), the cost to HCPs from increasing demand for or use of services, and costs to users (intervention participants and their social supporters). The cost of developing and delivering the intervention will be estimated in consultation with the app developers, data from the pilot study, the maintenance team, time and motion studies conducted at representative sites over a 2-week period, as well as administrative records during implementation. The costs of maternity service use to access care will be collected from all aim 1 participants and HCPs at exit; all intervention users and HCPs will provide the cost of care seeking and intervention involvement. We will identify comprehensive tasks required by both users (eg, time used to seek care) and HCPs (eg, training and staff time) and quantify public-sector resource use during the use and provision of the HCP-led service during the 3 years of implementation. Routine and additional public-sector unit costs will be collected from the health management information system [100] and administrative records at the facility and district levels, MOH, and other safe motherhood implementing partners. Direct and indirect costs to intervention users and HCPs because of involvement in the intervention (such as trainings, time used to seek care, and time used by HCPs to enroll users on the app) will be collected from participant exit interviews and administration records. The costs of providing user phones and solar chargers will be explored.

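### If the arms prove equivalent, the planned cost-minimization analysis reports a cost for Support-Moms alone, so it cannot show which option is cheaper

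*Protocol article*

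**What the plan says.** The fallback is in the Study Overview of the protocol article: "if Support-Moms and standard of care are found to have equivalent effectiveness, we will conduct a cost-minimization analysis". Its content is then fixed: "only the cost of Support-Moms per participant will be estimated and reported", with the added statement that "no incremental cost-effectiveness ratios [ICERs] will be calculated". The purpose is given in the next sentence: "This alternative approach would remain informative to the policy makers and stakeholders in maternity service use".

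The Aim 3 section sets the general plan, with no exception for equivalence: "The incremental cost and the cost-effectiveness of the Support-Moms intervention or program will be estimated from HCP and health system and societal perspectives". The costs to be measured are those of developing and running the programme, those borne by users, and "the cost to HCPs from increasing demand for or use of services". On data, "The costs of maternity service use to access care will be collected from all aim 1 participants and HCPs at exit", which covers both randomized arms.

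The Cost-Effectiveness Analysis section adds a decision tree that carries expected costs and outcomes for Support-Moms and for routine care.

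**The concern.** Once two options are accepted as equally effective, the comparative economic question is which one costs less. That needs a cost for each option, or the difference between them. The Study Overview names a method that makes this comparison and then prescribes a calculation that does not. The word *only* makes this a stated rule; it is not a detail left for an analysis plan to supply.

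At stake is the use of the result. The Ministry of Health is the intended audience, and the protocol says the fallback would still inform it. As written, the Ministry would get a cost per participant with nothing to set it against. It could not tell an app that pays for itself through lower care costs from one that adds to them.

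**Working it through.** **Nothing to reproduce.** The documents give no cost figure for either arm. The check is therefore a reading of the sections side by side, plus an identity.

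**Identity.** Per woman, let c be the programme cost, S1 the mean service-use cost (provider and user) in the Support-Moms arm, and S0 the same in the routine-care arm.

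- Total cost, Support-Moms: c + S1
- Total cost, routine care: S0
- Incremental cost: (c + S1) − S0 = c − (S0 − S1), which is programme cost minus the net saving in service use

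**What the fallback reports, under each reading of the cost of Support-Moms.**

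1. Programme cost only: the report gives c. Both S1 and S0 are absent.
2. Whole intervention-arm cost, using the three components named under Aim 3: the report gives c + S1. S0 is absent.

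S0 is missing either way, so the incremental cost cannot be formed.

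**Illustration of reading 1 (assumed values, arbitrary units; none come from the documents).** Take c = 10.

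| Net saving in service use (S0 − S1) | Incremental cost (10 − saving) | Reported programme cost |
|---|---|---|
| −10 | +20 | 10 |
| 0 | +10 | 10 |
| 5 | +5 | 10 |
| 10 | 0 | 10 |
| 20 | −10 | 10 |
| 30 | −20 | 10 |

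One reported figure is compatible with Support-Moms being dearer, neutral or cheaper. Under reading 2 the reported figure moves with S1, but for any given value of it the sign still turns on the unreported S0.

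**Could S0 − S1 be taken as zero?** Only then would c equal the incremental cost. The protocol does not expect it. The Aim 3 section budgets for provider costs from greater demand, and the Discussion expects the approach to recoup later costs of preventable maternal illness and death. The primary effectiveness outcome is skilled birth; equal skilled-birth rates would not by themselves make antenatal visits, complications, travel or users' time equal.

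**Sections side by side.**

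| Section | Routine-care cost or cost difference? |
|---|---|
| Study Overview, equivalence branch | Neither |
| Aim 3 | Incremental cost promised; service-use costs from both arms |
| Cost-Effectiveness Analysis | Expected costs modelled for both options |

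The comparison is planned in general and then excluded in the one branch where effectiveness no longer separates the arms.

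**The case against.** The best defence is that Support-Moms is an add-on. The section on intervention delivery says that women in that arm also receive standard routine care, so a cost per participant could stand for the extra cost. What stands is that this is a useful affordability figure and worth reporting. As an incremental cost it holds only if service-use costs are equal between arms, which the protocol's own expectations make doubtful.

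A second defence is that the sentence is loosely worded: *only* may mainly contrast costs with ratios, and a conditional exception does not by itself contradict a general plan. That is fair as far as it goes, and dropping the ratios under equivalence is reasonable. But the sentence limits what is estimated as well as what is reported, and Aim 3 acknowledges no exception.

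Three stronger readings are tempting and not supported:

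- *That changes in care use necessarily drop out of the figure.* The Study Overview does not say programme cost, and Aim 3 counts provider and user costs too. Extra visits in the intervention arm may be inside the figure. What is clearly absent is the comparator.
- *That the omission can be sized from the pilot.* Scaling the pilot contrasts to 412 per arm gives (10/40 − 3/40) × 412 ≈ 72 fewer women with complications and (40/40 − 20/40) × 412 = 206 more with at least four antenatal visits. Those arms were far from equivalent (98% against 70% skilled delivery), so their contrasts cannot be carried into a branch that presupposes equivalence. They also rest on 40 women per arm.
- *That routine-care costs would not be gathered.* Aim 3 collects service-use costs from all trial participants. The fault is in the estimation and reporting rule.

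**Conclusion.** The concern holds in this form: in the equivalence branch, the stated calculation gives a cost for Support-Moms alone and cannot identify the cheaper option, and it does not fit the Aim 3 and Cost-Effectiveness Analysis sections. This is true on either reading of the cost of Support-Moms and does not depend on the illustrative values above.

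The size of the missing part is unknown, because the documents give no unit costs. The weight is moderate: this is a conditional branch of aim 3, the primary analysis is unaffected, and the sections can be reconciled by rewording. The conclusion takes a finding of equivalence as given; how a trial powered for superiority would establish one is a separate matter.

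**What to change.** Amend the fallback sentence in the Study Overview. Keep the rule that no incremental cost-effectiveness ratios are calculated. Replace the one-arm figure with:

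- mean total cost per woman in each arm (programme, provider and user costs as defined under Aim 3);
- the incremental cost, with a 95% confidence interval, or an uncertainty interval where unit costs are modelled;
- both for each perspective named under Aim 3, with the programme cost per participant shown beside them.

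The choice of interval method can be left to the analysis plan.

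The text change is a sentence or two, and it draws on costs that the plan already collects or models for both arms. It is not free: public-sector unit costs come from the health management information system and administrative records, and delivery costs partly from time-and-motion work at representative sites, so some effort is needed to apply them to individual women's service use. The interval will probably be wide, and a wide interval should be reported as such. The article expected the last participant to exit in March 2026 and data collection to end in March 2027, so when it was written there was time to make the change before analysis.

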**Figure 1 figure1:**
[figure not shown]
Modified conceptual framework by Proctor et al [66] for implementation and evaluation.

### Study Setting

Uganda’s public health system is organized into 7 tiers with national and regional referral hospitals, general district hospitals, and 4 levels of community HCs. Staffing and available services vary across the 4 levels; HC3 carry out vaginal deliveries, whereas HC1 and HC2 serve as low-resource referral units. HC4s and hospitals conduct normal and cesarean deliveries and have ambulances and blood transfusion services [68]. Private HCPs operate in parallel to the public health system to provide maternal health care. Mbarara District is located approximately 270 km southwest of the capital, Kampala [69]. Mbarara District hosts a regional referral hospital that serves the southwestern region (Mitooma district inclusive); most deliveries are high risk [70]. Mitooma District borders Congo and is situated approximately 370 km southwest of the capital [71]. These 2 sites were selected for this research based on their geographic, sociocultural, and institutional diversity and high maternal mortality and morbidity data (Table 1 presents more details). Both districts have publicly funded and operated facilities with an active maternity care unit. Participants may be seen at any of the maternity sites in these 2 districts or other neighboring districts (Table 1), with recruitment and follow-up organized through CHWs. This consideration, plus the diversity of the settings and the study population, has potential for generalizability to similar settings. The local economy of these 2 districts is also largely based on subsistence agriculture, with both food and water insecurity being common [72,73]; ANC attendance of ≥4 visits is still at 58%, and the skilled facility delivery rate is approximately 70%. Maternity services, including delivery, are largely provided free of charge through public HCs.

**Table 1 table1:** Mbarara and Mitooma district statistics 2019.

Characteristics	Mbarara, n	Mitooma, n
Total population	Approximately 250,000	Approximately 185,000
Annual registered ANC^a^ visits	31,200	18,350
Annual public facility deliveries	14,800	4450
MMR^b^ per 100,000 live births	328	412
Hospital availability	5 (4 are private)	0
Publicly funded HC4s^c^	2	1
Publicly funded HC3s	10	6
VHTs^d^	246	143
Other private facilities providing maternity services	34	12
Total HCPs^e^	253	104

^a^ANC: antenatal care.

^b^MMR: maternal mortality ratio.

^c^HC: health center.

^d^VHT: village health team.

^e^HCP: health care provider.

### Aim 1: Testing the Effectiveness of the Novel Support-Moms Intervention in a Randomized Controlled Trial

We will enroll a cohort of 824 adult pregnant individuals with gestational ages ≤20 weeks at enrollment (determined by last normal menstrual period or ultrasound scan where available). Consenting participants will be randomized 1:1 at enrollment to standard of care (Ministry of Health [MOH] guidelines–based routine care and information giving, n=412, 50%) versus the Support-Moms (intervention) group (n=412, 50%). We will identify, screen, and enroll people through the existing CHWs or VHT structure from areas within a 10 km radius of all publicly funded maternity centers across Mbarara and Mitooma districts, who have not yet presented for ANC by the beginning of their second trimester. We will power the study to test the superiority of the Support-Moms intervention for our primary effectiveness outcome: HCP-led skilled birth delivery. Secondary outcomes will include (1) number of ANC visits, (2) institution-based delivery, (3) SS, (4) mode of infant delivery, (5) all deaths (maternal, fetal, and newborn), (6) preterm birth, (7) birth weight, (8) breastfeeding, (9) completion of postnatal care, and (10) complications of pregnancy and childbirth (eg, obstructed labor, ruptured uterus, need for neonatal or maternal resuscitation or assisted ventilation, severe preeclampsia or eclampsia, postpartum hemorrhage, maternal or newborn sepsis, and other infections).

### Recruitment and Enrollment of Study Participants

We will include individuals who (1) are in the first trimester of pregnancy and have not yet presented for ANC, (2) reside in the catchment area of a study HC, (3) are emancipated minors and adults aged ≥18 years, (4) report access to a cell phone with reception in their home, (5) are able to identify at least 2 social supporters living within the study districts, and (6) are able to provide consent. Notably in our pilot study, >95% of screened individuals had access to a cell phone, and all were able to identify at least 2 social supporters living within their communities [63]. We will track the exclusion rates to inform generalizability. CHWs will notify study research assistants (RAs) about potentially eligible participants, who will then contact and seek written informed consent and assent for emancipated minors (ie, those aged <18 years and pregnant) before enrollment into the study. Participants will be asked to identify 2 individuals from their existing SS network with whom they have had stable, long-term relationships and believe they would be available to help them during the pregnancy and study follow-up period. Eligible social supporters will include spouses, relatives, CHWs, and friends [23-25] aged ≥18 years; who are aware that the study participant is pregnant; and who own a cell phone for personal use with reported reliable reception. Potential social supporters will be excluded from the study if they are unable to use SMS or are unwilling to receive SMS notifications, as this was identified as a barrier in the pilot study. In the pilot study, one of the eligible social supporters identified by women included a spouse (75%), friend (38%), sibling (10%), parent (53%), and a CHW (25%), and we expect a similar distribution in the trial. There will be no gender exclusion criteria for social supporters. We will emphasize the selection of an existing partner, who is aware of the pregnancy, as one of the social supporters. This was not a problem in our pilot study, as most women were able to suggest a partner as a potential social supporter, alongside a friend, sibling, parent, or CHW. A few partners were excluded because they did not own a cell phone for personal use (5/40, 13%) or were not aware of the pregnancy (5/40, 13%). All other eligible social supporters that were identified by participants in the social supporter arm (80/80, 100%) were successfully enrolled and completed study procedures. RAs will contact social supporters from the intervention arm within 2 weeks of the enrollment of pregnant women to confirm an active relationship at the time of their enrollment. Eligible social supporters will be offered an explanation of the study procedures and an opportunity to participate in informed consent. The study nurse will inform consenting social supporters about the objectives of ANC and skilled delivery as well as danger signs during pregnancy using standard MOH and WHO guidelines [9,74].

### Randomization

Before the study initiation, the study statistician will generate a randomization table, inaccessible by other study team members, and lock it and store it in the REDCap (Research Electronic Data Capture; Vanderbilt University) study database. Participants will be stratified according to district and HC level and randomly assigned to either intervention or control arms in a ratio of 1:1 in blocks of 10. RAs will be informed of the arm assignment by the REDCap module after consent and at the time of enrollment. Study participants in the control group will receive MOH guidelines–based routine care and information giving. The intervention group will receive the intervention described in the next section.

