### Data Collection

Baseline participant characteristics will be collected from study participants from both arms as well as among the social supporters in the intervention arm physically (Table 2). Data collected through participant questionnaires will be conducted in the local languages, Runyankole and Rukiga. We will collect outcome data in two ways: (1) through medical record review of the routinely provided ANC cards, postnatal discharge forms (where available), and records at the relevant HCs and (2) through participant exit interviews 2 to 4 weeks following delivery to enhance data completion, particularly for people who did not deliver at a facility.

**Table 2 table2:** Baseline questionnaire items for study participants and social supporters.

Topic		Details of measure

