## Results

This study was funded in September 2023. Ethics approval was obtained in February 2024, and actual data collection started in March 2024. As of January 2025, 75% (618/824) of all projected study participants have consented and been recruited into the study. Participants are expected to be followed up until delivery, and 15% (124/824) of the participants have exited to date. Data analysis for the trial is expected to start as soon as the last participant exits (expected in March 2026). The qualitative interviews will start in April 2025, and data will be analyzed and published as soon as data collection is done. Data collection is expected to be completed by March 2027.

We are currently recruiting at least 60 women or individuals and their social supporters per month. We have registered no loss to follow-up so far.

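### A single block size of 10, with recruiting staff who see every arm, leaves some upcoming allocations predictable; varied, undisclosed sizes of 8, 10 and 12 would remove almost all the certain ones

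*Protocol article*

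**What the plan says.** The Randomization section of the protocol article has the statistician "generate a randomization table, inaccessible by other study team members, and lock it and store it in the REDCap" study database. It then states that "Participants will be stratified according to district and HC level" and are "randomly assigned to either intervention or control arms in a ratio of 1:1 in blocks of 10". One block size is given, with no mention of variation. The same section says "RAs will be informed of the arm assignment by the REDCap module after consent and at the time of enrollment".

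Under Recruitment and Enrollment of Study Participants, the same staff do the recruiting: "CHWs will notify study research assistants (RAs) about potentially eligible participants, who will then contact and seek written informed consent". Control women receive routine care without the app and no masking is described, so the arm is evident once it is released.

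The Results section reports 618 of 824 women recruited by January 2025, and "We are currently recruiting at least 60 women or individuals and their social supporters per month".

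**The concern.** Hiding the list stops anyone from looking up an allocation. It does not stop someone from inferring the next one from those already seen. With one fixed block size, few strata and unmasked recruiters, a running tally shows which arm is behind and, near the end of a block, which arm must come next.

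An assistant with that knowledge could choose when to approach a woman thought more or less likely to deliver with a skilled attendant. The assistant could also be stricter or looser on criteria that rest on report, such as phone access at home and naming two supporters. None of this need be deliberate. At stake is the comparability of the arms on the primary outcome, which randomization is meant to guarantee and which adjustment for age, high-risk pregnancy and facility would restore only in part.

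**Working it through.** **Inputs.** Block of 10, 1:1, so m = 5 per arm (Randomization). Total 824, with 618 recruited, so 824 − 618 = 206 remained (Results). At 60 per month, 206/60 ≈ 3.4 months of recruitment. The numbers of strata and of assistants are not given; 4 to 6 strata is an assumption.

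**Plan's own figures.** The plan gives no figure for predictability. Its sample size is not in dispute: 70% against 80%, two-sided 5%, 90% power gives 392 per arm, 784 in total. Allowing for 5% loss gives 784 × 1.05 ≈ 824, or 784/0.95 ≈ 826.

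**Certain allocations, fixed block.** For someone who knows the block size and sees every allocation in the stratum, the expected number of forced allocations at the end of a block of 2m is 2m/(m + 1):

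- 10/6 = 1.67 per block of 10, or 16.7%
- over the whole trial: 824/6 ≈ 137
- among women not yet recruited in January 2025: 206/6 ≈ 34

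**Best-guess rate, fixed block.** Always guessing the arm that is behind gives m + 2^(2m−1)/C(2m, m) − 1/2 correct guesses per block:

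- 5 + 512/252 − 0.5 = 6.53 of 10, or 65.3%

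**Varied block sizes.** Guessing the arm that is behind needs no knowledge of block size, because every block ends balanced. The same formula gives 2.83, 4.10, 5.33, 6.53 and 7.72 correct for blocks of 4, 6, 8, 10 and 12. With sizes equally likely:

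| Scheme | Average guess rate | Certain allocations |
|---|---|---|
| Fixed 10 | 65.3% | 16.7% |
| 4, 6, 8, 10 | (2.83 + 4.10 + 5.33 + 6.53)/28 = 67.1% | about 1% |
| 8, 10, 12 | (5.33 + 6.53 + 7.72)/30 = 65.3% | about 1% |

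The figures of about 1% come from simulating an observer who sees every allocation in a stratum and even knows the set of sizes, but not their order. Simulated guess rates agree with the formula: about 67% for the first mix and 65% for the second.

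**Illustrative effect on the result.** Let d be the difference in skilled-birth probability, in percentage points, between the women an assistant would favor and those the assistant would not. The values of d are assumptions.

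- Steering every allocation on the best guess: bias = (0.653 − 0.347)d ≈ 0.31d, that is 0.6, 1.5 and 3.1 points for d = 2, 5 and 10.
- Steering only when certain: bias = 0.167d, that is 0.3, 0.8 and 1.7 points. With about 1% certain, it is about 0.01d, at most 0.1 point for these d.

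These are worst cases, set against a planned difference of 10 points. The change of list removes the second kind of steering and leaves the first about where it was.

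**The case against.** The strongest reply is that concealment is already good. The statistician holds a locked table, REDCap releases the arm only after consent, community health workers rather than assistants identify candidates, and eligibility is settled before the current woman's arm is known. Ten is also a fairly long block. The 16.7% and 65% require one person to see and log every allocation in a stratum. Recruitment covers the catchments of many centers (Table 1 lists 2 + 10 + 1 + 6 = 19 public HC3 and HC4 sites), so several assistants may share a stratum. All of this stands. It makes the figures ceilings, but it does not prevent prediction of the next allocation.

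A second reply is that varying the block size does not lower the average guess rate. That also stands, and it decides the choice of sizes: a 4/6/8/10 mix would raise the rate to about 67%, while 8/10/12 holds it at 65%. The gain is in the certain allocations only.

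Two stronger readings are tempting but unsupported. A reader might infer that the arm is released before the baseline questionnaire, so that answers on social support, depression or high-risk history carry knowledge of the arm. The article says only that women are randomized after consent and at enrollment, and that "Baseline participant characteristics will be collected from study participants from both arms as well as among the social supporters in the intervention arm physically". It gives no order for the women's questionnaire, and an article commonly leaves form sequence to the full protocol. A reader might also infer that the block size was made public while recruitment ran. The text gives status at January 2025 but no publication date, and only about 3.4 months of recruitment remained. The guess rate does not depend on knowing the block size in any case.

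**Conclusion.** The concern holds for prediction of upcoming allocations. One fixed block size, combined with recruiters who see each arm, lets a person who tracks a whole stratum know up to 16.7% of allocations (about 34 of the 206 women outstanding in January 2025) and guess about 65%. Both rest on complete tracking by one person and on whole blocks. They fall, by an amount the article does not allow one to estimate, when assistants share a stratum. No actual steering is shown.

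Contamination of baseline data and publication of the block size during recruitment are not established and form no part of the conclusion. The weakness is modest and cheap to reduce while any women remain to be randomized.

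**What to change.** For any remaining allocations, starting at the next block in each stratum, have the statistician load a list with block sizes of 8, 10 and 12 in random order, not disclosed to recruiting staff. Sample size and ratio do not change. The cost is one replacement list and slight possible imbalance at the ends of strata.

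As a secondary safeguard at little or no cost, set REDCap to release the arm only after the eligibility and baseline forms are saved. For women already enrolled, use the time stamps to report the actual order of baseline and allocation.

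If recruitment has closed, the list can no longer be changed. The report should then say whether assistants knew the block size, and show screening and consent by assistant and stratum.
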